#### sEMG data analysis

2.11.2

To process the sEMG signals, a high-pass filter with a cut-off frequency of 20 Hz will be applied, followed by rectification using the Hilbert transform to generate sEMG envelopes (Allen et al., 2020). The envelopes obtained from repeated trials will be averaged across different experimental paradigms and used for muscle synergy and muscle network analyses. Muscle synergies will be extracted using NNMF and PCA. Both methods will be employed to determine the number of muscle synergies (Bekius et al., 2020; Boonstra et al., 2015), synergy complexity (d'Avella and Bizzi, 2005), and muscle synergy sparseness (Cheung et al., 2020). The analysis will be conducted using Matlab 2019a (MathWorks Inc., Natick, Massachusetts, USA). NNMF is a technique that decomposes a data matrix (*A*) into two non-negative matrices: a command matrix (*K*) and a synergy matrix (*W*), ensuring that all components remain non-negative. PCA, on the other hand, identifies orthogonal principal components (PCs) that represent the most significant variance within the EMG dataset (Yin et al., 2015; Jolliffe and Cadima, 2016). These PCs reflect collective muscle activation patterns and their overall contribution to data variability. Using PCA and NNMF allows for a comprehensive understanding of potential synergies across different experimental conditions. To evaluate muscle synergy complexity, the total variance accounted for by a single synergy solution (tVAF1) will be computed, as it is associated with muscle function. For assessing muscle synergy sparseness, a sparse synergy vector containing a single non-zero component will be assigned a sparseness value of 1, whereas a non-sparse synergy vector, in which all muscles contribute equally, will be assigned a sparseness value of 0 (Cheung et al., 2020). Furthermore, significantly active muscles will be identified based on a loading coefficient exceeding 0.5 within a given PC. The frequency of significantly activated muscles for each PC will be analyzed based on different experimental paradigms. Muscle network analysis will also be performed using intermuscular coherence and partial directed coherence (PDC) to evaluate functional connectivity among muscles. The HERMES toolbox will be used to estimate connectivity between different sEMG envelopes (Boonstra et al., 2015). Coherence and PDC analyses will be conducted to assess undirected and directed connectivity patterns.

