**Discussion:**

The results of this trial will clarify the efficacy of DLPFC-tDCS in enhancing M1-DLPFC functional connectivity and improving trunk muscle synergy patterns. These findings will provide a theoretical foundation for developing new therapeutic targets for the treatment of cLBP.

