##### Muscle synergy

2.10.2.1

Muscle synergies will be assessed using wireless surface electromyography (sEMG) (Trigno, Delsys, Inc., USA). To optimize electrode conductivity, thorough skin preparation will be performed before electrode placement. The muscle activity of the erector spinae (ES), multifidus (MF), rectus abdominis (RA), and bilateral transversus abdominis (TA) muscles will be recorded (as shown in Table 2). Electrode placement will follow the standardized guidelines recommended in previous studies (Hermens et al., 2000; Park et al., 2014). The extraction of muscle synergies will be carried out using non-negative matrix factorization (NNMF) and principal component analysis (PCA) (Bekius et al., 2020; Rabbi et al., 2020; Wang et al., 2015). The analysis will include measurements of the muscle synergies number, complexity, sparseness, clusters, and muscle networks.

**Table 2 tab2:** Placement of the sEMG electrodes.

Muscle	Electrode placement location
Transversus abdominis (TA)	Along either side of the course of the underlying muscle fibers and centered 2 cm cephalic to the pubic bone, just lateral to the midline, and parallel to the superior pubic ramus
Rectus abdominis (RA)	2 cm lateral from the midline of the umbilicus
Multifidus (MF)	A line from caudal tip posterior spinal iliac superior to the interspace between L1 and L2 interspace at the level of L5 spinous process (i.e., about 2–3 cm from the midline)
Erector spinae (ES)	2 cm lateral to the L3 level

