#### Statistical analysis

2.11.1

Statistical analyses will be performed using SPSS (version 25.0, IBM, USA). Before performing descriptive statistics, the Shapiro–Wilk test will be applied to evaluate the normality of data distribution. Data following a normal distribution will be reported as mean and standard deviation (SD), while non-normally distributed data will be expressed as medians with interquartile range (IQR). Categorical variables will be summarized as percentages and frequencies. Baseline demographic and clinical characteristics will be compared between groups using appropriate statistical tests based on the data type. Continuous variables that follow normal distribution will be analyzed while using independent sample *t*-tests, whereas non-parametric Mann–Whitney *U*-tests will be applied for non-normally distributed continuous data. Categorical variables will be analyzed using chi-square tests or Fisher’s exact tests, as appropriate. Correlations between variables will be evaluated using the Pearson correlation coefficient or Spearman correlation coefficient based on the type of data. A repeated-measures analysis of variance (2 groups × 4 time points) will be performed to assess the therapeutic effects on primary and secondary outcomes. If a significant main effect was observed, *post hoc* tests with Bonferroni correction were conducted. A *p*-value of <0.05 will be considered statistically significant.

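### Synergy number, complexity and sparseness are each obtained by two unranked extraction methods and tested at p < 0.05 with no control across them, so the planned synergy conclusion carries more than a 5% chance of a false positive

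*Protocol article*

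**What the plan says.** All references are to the protocol article.

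- **Measures.** Section 2.10.2.1 (Muscle synergy, a secondary outcome) states: "The analysis will include measurements of the muscle synergies number, complexity, sparseness, clusters, and muscle networks".
- **Methods.** Section 2.11.2 states: "Muscle synergies will be extracted using NNMF and PCA". It continues: "Both methods will be employed to determine the number of muscle synergies", and the same sentence extends this to complexity and sparseness. Complexity is the variance accounted for by a one-synergy solution (tVAF1). The section adds the frequency of active muscles per principal component, intermuscular coherence and partial directed coherence (PDC).
- **Test and threshold.** In section 2.11.1 a repeated-measures ANOVA ("2 groups × 4 time points) will be performed to assess the therapeutic effects on primary and secondary outcomes") is the only efficacy test. The criterion is: "A *p*-value of <0.05 will be considered statistically significant".
- **Multiplicity.** The only correction follows a significant main effect: post hoc "tests with Bonferroni correction were conducted".
- **Association.** Section 2.11.1 provides Pearson or Spearman correlations between variables and names none of them.
- **Claim.** The abstract's Discussion says the results "will clarify the efficacy of DLPFC-tDCS in enhancing M1-DLPFC functional connectivity and improving trunk muscle synergy patterns". Section 3.1 (Summary) looks forward to a similar conclusion.
- **Hypotheses.** The last paragraph of the Introduction makes the link between abnormal synergy and reduced M1-DLPFC connectivity the primary hypothesis. The effect of stimulation on surface EMG (sEMG) falls under the secondary objective.

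**The concern.** The word synergy stands for several quantities here, and three of them are produced twice, once per extraction method. Each result meets the same 0.05 threshold. The article does not say which result the synergy conclusion rests on, or how to read it if NNMF shows a group difference and PCA does not.

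Two things are at stake. First, a statement that DLPFC stimulation improved synergy could rest on whichever of several results crosses 0.05, with a false-positive risk above the nominal level. Second, the correlation analysis behind the primary hypothesis draws on the same set of synergy measures. It names neither the synergy variable nor any adjustment, so the variable could be chosen after the data are seen.

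**Working it through.** The documents give no error rate for the synergy outcome, so there is no figure of theirs to reproduce.

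**Inputs from the article**
- Per-test threshold: 0.05 (section 2.11.1). Sidedness is not stated there; two-sided is assumed, so c = 1.96.
- Measures obtained by both methods: number, complexity, sparseness, so 3 (section 2.11.2).
- Methods: NNMF and PCA, so 2 (section 2.11.2).

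**Assumed inputs**
- One group comparison per result.
- A common correlation ρ between test statistics, varied from 0 to 0.95. The documents give none.
- Tasks pooled, so no multiplication by task.

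**Count.** 3 measures × 2 methods = 6 tests. Clusters, component muscle frequencies, coherence and PDC are left out.

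**Does the stated correction cover these six?** No. Bonferroni acts on post hoc comparisons within one ANOVA. It does not act across ANOVAs for different measures or methods.

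**Independent tests.** P(at least one false positive) = 1 − (1 − 0.05)^6 = 1 − 0.735 = 0.265.

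**Equally correlated tests.** With φ and Φ the standard normal density and distribution function,

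P = 1 − ∫ φ(u) [Φ((c − √ρ·u)/√(1−ρ)) − Φ((−c − √ρ·u)/√(1−ρ))]^6 du

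| Assumed ρ | P(at least one false positive), 6 tests | Multiple of 5% |
|---|---|---|
| 0 | 26.5% | 5.3 |
| 0.5 | 20.7% | 4.1 |
| 0.8 | 13.9% | 2.8 |
| 0.9 | 10.8% | 2.2 |
| 0.95 | 8.9% | 1.8 |

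**Other count.** Adding coherence and PDC as one result each gives 6 + 2 = 8 tests: 33.7%, 25.0% and 15.7% at ρ = 0, 0.5 and 0.8.

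**After the change.** With one named measure from one method, the risk for the synergy claim is 0.05. Bonferroni across the six would instead need 0.05/6 = 0.0083 per test.

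**The case against.** **Secondary outcome, condensed article.** Secondary outcomes are often tested at 0.05 and read as supportive. A ranking of measures and a rule for disagreement could sit in a fuller protocol or analysis plan that is not shown. This has weight, and silence alone would be no finding. What remains is that the article does fix a threshold, confines its only correction to post hoc tests, prescribes two unranked methods and announces an efficacy conclusion on synergy. Nor does it say that one significant result on any measure counts as improvement; the point is that nothing it states prevents that reading.

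**Correlation.** Both methods work on the same envelopes for the same three quantities, so paired results could correlate above 0.8. This stands: 14% is not a floor, and the range must extend down to about 9%.

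**Tasks.** Section 2.10.2.3 lists three tasks with left/right, arm/leg and stance variants. A reader might infer 6 × 3 = 18 tests, or 6 × 8 = 48 if each variant is counted, with much higher error rates. The document does not establish this. Section 2.11.2 says envelopes are averaged across experimental paradigms before the synergy and network analyses, which may mean that tasks are pooled. The same section analyses component muscle frequencies by paradigm, so the matter is open.

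**Main conclusion.** A reader might also infer that these rates apply to the trial's primary objective. They do not. That objective is an association between connectivity and synergy, whereas the rates concern a treatment effect under the secondary objective. For the association, the documents support only the observation that the variables are unnamed and unadjusted. The remark in section 3.2 that only data-level fNIRS-sEMG analyses are possible does not name them either.

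**Conclusion.** The concern holds in a limited form. Under the article's stated rules, a conclusion of improved synergy has roughly a 9% to 27% chance of at least one false-positive result among six tests, about 21% at a correlation of 0.5. This rests on two-sided tests, one group comparison per result, pooled tasks and an assumed common correlation. Counting the omitted measures, or testing by task, would raise it by an amount the documents do not allow one to fix. The consequence is for the announced synergy conclusion and for the choice of variable in the connectivity correlation. It does not touch the pain, disability or mental health outcomes.

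**What to change.** 1. In section 2.11.2, name one key synergy measure from one extraction method as the sole basis for the synergy claim. tVAF1 from NNMF is one example: the section already describes tVAF1 as related to muscle function, but the choice belongs to the investigators.
2. Compute it on the task-averaged envelopes, or on one prespecified task if tasks are not pooled, and state which.
3. Compare its change from baseline to 3 weeks between groups. This fits the abstract, where secondary outcomes are assessed before and after the intervention.
4. In section 2.11.1, name the same measure for the correlation with M1-DLPFC connectivity.
5. Make the other extraction method a sensitivity analysis, so that disagreement has a defined reading.
6. Report all other synergy measures and correlations as exploratory, with estimates and intervals, or under Holm or FDR control.
7. Limit the conclusion in the abstract and section 3.1 to the key measure.

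The cost is wording only: no extra participants, visits or recordings, and no measure is dropped. The downside is that a finding seen only on another measure becomes exploratory.

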#### fNIRS data analysis

2.11.3

The NirSpark software package will be employed to preprocess fNIRS data. Initially, raw fNIRS signals will be transformed into optical density changes by applying a logarithmic transformation. Channels with excessively low optical intensity (coefficient of variation > 10%) will be removed to eliminate noise. A bandpass filter will be applied to minimize physiological artifacts and instrumental noise, with high-pass and low-pass cut-off frequencies set at 0.01 Hz and 0.1 Hz, respectively. Changes in [HbR] and [HbO] concentrations will then be determined using the modified Beer–Lambert law. To analyze cerebral cortical activity during tasks, a general linear model (GLM) will be used, represented by the equation:

Δ[Hbx]=X×β+ε

where Y represents the variation in [HbR] or [HbO] concentration, X denotes the modeled neural response predicted based on task onset and convolved with a classical hemodynamic response function, β is the regression coefficient reflecting the activation level of each channel, and ɛ accounts for unexplained variability or noise in the data. The β-value (μmol), which quantifies activation at each channel, will be calculated alongside the standard errors for [HbR] and [HbO] in both groups for each trial.

### Data collection, management, and monitoring

2.12

Data collection will be performed by experienced attending physicians, therapists, and researchers who are independent of the treatment allocation and intervention procedures. All collected data will be promptly recorded in designated case report forms (CRFs). A designated researcher will digitize the data while ensuring patient privacy and data security through unique identifiers. Two data managers, who will remain blinded to group assignments, will independently process the completed CRFs and enter the data into an Excel database. To maintain data integrity, both data managers will undergo comprehensive training in data monitoring and entry procedures.

To reduce the probability of an adverse event, the participants will be rigorously screened in accordance with the exclusion and inclusion criteria. Adverse effects and events will be closely monitored during the clinical trial. If this occurs, it will be noted in the CRF. Some incidents will be monitored, and when these incidents are inappropriate, the treatment will be discontinued, such as exacerbation of the condition, serious adverse events, poor adherence leading to a loss of follow-up or the development of a new serious illness affecting the course of this protocol.

### Quality control

2.13

The steering committee will oversee quality control throughout the trial. Before their involvement in the study, all researchers will receive training in professional trial methods and routine monitoring techniques to ensure methodological consistency. If any modifications or corrections are made to the study protocol, the steering committee and ethics committee will be notified accordingly. Regular monitoring will be conducted to ensure adherence to the study protocol and the integrity of collected data.

## Discussion

3

### Summary

3.1

This study presents the protocol for an RCT designed to assess the efficacy of tDCS targeting the DLPFC in patients with cLBP. The trial aims to determine whether DLPFC-tDCS can improve activity and functional connectivity between the M1 and DLPFC. The results of this study will provide critical insights into the potential therapeutic role of DLPFC-tDCS in improving M1-DLPFC connectivity and trunk muscle synergy, forming a theoretical foundation for novel treatment approaches for cLBP. Previous research has used multivariate pattern analysis and fMRI to identify disruptions in functional connectivity among key brain networks in cLBP patients. These networks include salience, sensorimotor, the default mode, and central executive networks. Findings suggest that the rostral anterior cingulate cortex and medial prefrontal cortex may serve as critical hubs associating the default mode network with other neural circuits in individuals with cLBP (Tu et al., 2019). Furthermore, a study published in *NeuroImage* demonstrated that the DLPFC has extensive anatomical projections to M1 and that these two regions interact closely during motor tasks. This suggests that exercise-induced neuroplasticity may result from altered input from the DLPFC to M1 rather than the training effect within M1 itself (Cao et al., 2022). These findings highlight the relevance of M1-DLPFC functional connectivity in motor control and muscle coordination.

To the best of our knowledge, this study will be the first to investigate the pathological mechanisms of cLBP by examining brain connectivity and trunk muscle synergy. We hypothesize that the abnormal coordination patterns observed in trunk muscles in cLBP patients are not only a result of adaptive changes within M1 and DLPFC but also due to reduced functional connectivity between these regions. This connectivity impairment may play a key role in the neuromuscular dysregulation of trunk muscles in cLBP. By comparing the therapeutic effects of M1-tDCS and DLPFC-tDCS, we expect that M1-tDCS will primarily increase M1-supplementary motor area (SMA) connectivity, while DLPFC-tDCS will strengthen M1-DLPFC functional connectivity. This improvement in connectivity is expected to restore trunk muscle coordination and improve clinical symptoms.

### Strengths and limitations

3.2

One of the major strengths of this protocol is that it represents one of the first clinical trials investigating the efficacy of DLPFC-targeted tDCS in patients with cLBP. If proven effective, DLPFC-tDCS could serve as a viable therapeutic option for managing cLBP. Another advantage of the study is its potential to reveal the neuroregulatory mechanisms underlying the functional connections between brain regions and their impact on trunk muscle coordination in cLBP patients.

However, there will be some limitations. A key limitation is the absence of a healthy control group. Including healthy participants would allow for a more comprehensive comparison with the M1-tDCS and DLPFC-tDCS groups, improving the interpretation of the results. Moreover, differences in the sampling rates of the two fNIRS systems used during measurements present a methodological challenge. Since the sampling rates of fNIRS and sEMG differ, direct correlation analyses between their signals cannot be performed. Instead, only data-level analyses can be conducted, which may limit the ability to fully capture the relationship between cortical activity and muscle activation patterns.
